### Study organisation

The study is being conducted across approximately 53 study sites in 14 countries. The anticipated numbers of patients per country are as follows: Croatia, 355; Denmark, 620; Finland, 100; France, 150; Germany, 135; Israel, 350; Italy, 130; Netherlands, 100; Poland, 200; Romania, 60; Spain, 375; and UK, 300. Additional countries and study sites might be included during the study period. Sites have relatively similar standard routine procedures with regard to the treatment of women with diabetes during pregnancy and have a relatively high prescription rate of IDet. The projected study timeline is given in Fig. 2.

**Fig. 2 Fig2:**
[figure not shown]
Study timeline. FPFV, first patient first visit; LPFV, last patient first visit; LPLV, last patient last visit

The study is sponsored by a research grant from Novo Nordisk A/S. A Novo Nordisk A/S internal safety committee will perform ongoing safety surveillance. The study will be conducted in accordance with Good Pharmacoepidemiology Practice and the Declaration of Helsinki, and has been approved separately in each of the participating countries (national health authorities/local institutional review boards/independent ethics committee). Written informed consent is required from all study participants. The trial registration number is NCT01892319 (www.clinicaltrials.gov).

## Discussion

Outside of pregnancy, long-acting insulin analogues improve glycaemic control, and are associated with lower rates of hypoglycaemia than human insulins [14, 15]. Among the insulin analogues, the European Union labels for both IDet and IGlar allow for consideration of use in pregnancy [16, 17]. In the case of IGlar, this is based on postmarketing data; for IDet, an RCT has been performed, demonstrating significantly lower FPG and non-inferior HbA_1c_ in late pregnancy and similar rates of hypoglycaemia compared with NPH insulin [7].

However, none of these studies were sufficiently large to accurately evaluate the incidence of events such as congenital malformations and perinatal/neonatal mortality in patients receiving insulin during pregnancy. Hence, this long-term, prospective, epidemiological study was initiated-the first of its kind in pregnant women with diabetes.

Although the primary endpoint is based around the incidence of malformation and mortality, the study will also examine a number of other important endpoints. For example, data on incidences of pre-eclampsia, fetal macrosomia and LGA will be collected. Each of these has been shown to occur more frequently in T1D than control pregnancies. Indeed, in a Swedish population study, odds ratios were 4.5 for pre-eclampsia and 11.4 for LGA [1].

Data on the incidence of maternal hypoglycaemia will also be examined in the present study, and compared between different insulin treatments. Severe hypoglycaemic episodes are common in diabetic pregnancy, particularly in the first trimester, and are associated with a variety of factors, including impaired hypoglycaemia awareness, long duration of diabetes, fluctuating plasma glucose values and excessive use of supplementary insulin injections between meals [18].

Furthermore, the study will also examine the health of the infant at 1 year of age, including the proportion with progression or regression of major congenital malformations, as well as early growth (height and weight) and breastfeeding history. Data on such outcomes are currently lacking, and so this trial is expected to fill an important gap in understanding.

The very liberal inclusion and exclusion criteria of this study mean that the population will be largely unselected, as compared with the highly selected populations typically eligible for RCTs. The results will therefore be more broadly applicable to the real-world population of pregnant women with diabetes. Furthermore, as the study collects data based on standard routine care, participation will be substantially less demanding on the women recruited, as compared with RCTs.

In summary, this is an international, prospective, non-interventional, multicentre, cohort study designed to assess the safety of IDet in comparison with other types of insulin treatment during pregnancy, and to monitor the health status of the resulting infants - who were exposed in utero - up to 1 year of age. The planned enrolment of 3075 patients is sufficiently large to allow comparison of the frequency of rare events, such as congenital malformations and perinatal/neonatal death, between the various insulin treatment regimens. The study will therefore provide valuable information on these events, as well as other relevant maternal, pregnancy and infant-related endpoints, to inform future prescribing with basal insulins in diabetic pregnancy.

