# Design and rationale of a large, international, prospective cohort study to evaluate the occurrence of malformations and perinatal/neonatal death using insulin detemir in pregnant women with diabetes in comparison with other long-acting insulins

**DOI:** 10.1186/s12884-016-1177-4

**Published:** 2017-01-18

**Keywords:** Diabetes, Pregnancy, Insulin detemir, Cohort study

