## Methods/design

This study is an international, prospective, non-interventional, multicentre cohort study to monitor and assess the safety of IDet in comparison with other types of insulin treatment during pregnancy, and to monitor the health status of the resulting infants (who were exposed in utero) at 1 month and 1 year of age. The large-scale data collection undertaken in this study will allow comparison and analysis of the occurrence of events between the various insulin treatment regimens. The same parameters will also be monitored for other injectable antidiabetic treatment regimens used during pregnancy.

The study is non-interventional. The assignment of patients to a particular therapeutic strategy is not decided in advance by a trial protocol but instead falls within current practice. Data will be collected in the context of routine practice, with very few exclusion criteria, and hence the results are expected to be more broadly applicable to the real-world population than those of typical RCTs.

The primary objective is to estimate the proportion of pregnancies in women treated with IDet, compared with other basal insulin regimens, which do not result in any of the following events: major congenital malformations, perinatal death or neonatal death (assessed at up to 4 weeks after delivery). The definitions of these and other key terms, within the context of this trial, are provided in Table 1.

**Table 1 Tab1:** Definitions of key terms

Term	Definition
Congenital malformation	A morphological defect of an organ, part of an organ or larger region of the body resulting from an intrinsically abnormal developmental process
Foetal macrosomia	Birth weight above 4 kg
Large for gestational age	Live born infant with birth weight >90th percentile for gestational age and sex according to local reference
Major malformation	A life-threatening structural anomaly or an abnormality likely to cause significant impairment of health or functional capacity and which needs medical or surgical treatment; examples are abnormalities likely to lead to serious handicap or likely to lead to major cosmetic defects (e.g., cleft lip) and which may require major surgery to repair (e.g., atrial septal defect or ventricular septal defect)

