### Statistical considerations

The analysis set will consist of all pregnancies among patients who are treated with basal insulin and have not changed basal insulin product for 4 weeks prior to conception and during pregnancy. Continuous variables will be summarised with descriptive statistics, and categorical variables will be displayed in frequency tables.

The primary endpoint will be analysed using a logistic regression model that will include treatment group, study site, race, hypertension, major hypoglycaemic events during pregnancy, folic acid intake and use of GLP-1 agonists during pregnancy as factors. HbA_1c_ at the start of pregnancy, the end of the first trimester and the end of the second trimester, age and body mass index at baseline, duration of diabetes, blood pressure and previous perinatal complications will be included as covariates. The primary endpoint will be computed for the IDet group and for the ‘other basal insulin’ group and the absolute difference between these proportions calculated, along with the 95% CI and the *p*-value using Fisher’s exact test.

For infant endpoints at 1 year, the proportions will also be analysed using logistic regression. Factors and covariates will be as per the primary endpoint. Analyses regarding height and weight will also be adjusted for exclusive and/or partial lactation period. Similar analyses will be performed for all other endpoints that are proportions.

Means of the continuous endpoints will be compared between the two groups using an analysis of covariance model.

The incidence of major hypoglycaemia during pregnancy will be computed for both treatment groups.

Observations of possible clinical importance (such as the primary endpoint split out according to diabetes type, insulin analogue or use of an insulin pump) will be presented using descriptive statistics.

All statistical analyses will be performed using appropriate statistical software, and tests will be performed as two-sided tests with a significance level of 0.05.

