### Determination of sample size

The sample size calculation was derived from the primary endpoint, based on patients with none of the three individual outcomes: major congenital malformations, perinatal death or neonatal death. The probability of this combination of endpoints is not known within the literature. However, based on data from a UK population study [10], which are in line with results from other European countries [1, 2, 4, 11–13], the proportion of pregnancies with any of the above outcomes is estimated at 8.2%: major congenital malformations, 4.5%; perinatal death, 3%; neonatal death, 0.9% (8.2% is computed under the assumption that the individual outcomes are independent). The proportion of pregnancies *without* any of the above outcomes is therefore estimated at 91.8%.

The goal is to be able to detect a difference of 3.5% between the proportions without the combined endpoint in the IDet group compared with the other basal insulin regimens group. Assuming a maximum 1:2 split between the two groups (IDet group: other basal insulin regimens group), a sample size of 1833 pregnancies is needed to have 80% power of achieving significance at a 5% level.

To achieve a total of 1833 pregnancies for the assessment of the primary endpoint, the planned number of patients to be included during the 5 years of the recruitment period is 3075. This number is based on the expectation that ~20% of pregnancies will result in a spontaneous abortion, ~10% will be treated with other antidiabetic injectables or will change basal insulin treatment and ~10% will be lost to follow-up, leaving 60% of pregnancies (i.e., 1833) assessable for the primary endpoint.

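### The Discussion's size claim covers single rare events across the various insulin regimens, but the sample size supports only the composite for detemir against all other basal insulins pooled

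*Protocol article*

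**What the plan says.** The closing paragraph of the Discussion describes the cohort, 3075 women in all, as "sufficiently large to allow comparison of the frequency of rare events, such as congenital malformations and perinatal/neonatal death, between the various insulin treatment regimens", and then says that the study will inform prescribing of basal insulins in diabetic pregnancy.

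The operative sections are narrower:

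- **Study endpoints.** The primary and key secondary endpoints set detemir against the other basal insulin regimens taken together. The Background counts both long-acting analogues and NPH as basal insulins.
- **Determination of sample size.** The aim is a 3.5-point difference "between the proportions without the combined endpoint in the IDet group compared with the other basal insulin regimens group", with a 1:2 split between those two groups. On that basis "a sample size of 1833 pregnancies is needed to have 80% power of achieving significance at a 5% level".
- **Statistical considerations.** The primary contrast gets a logistic model with many covariates and a Fisher's exact test. For further breakdowns of interest the section reads "such as the primary endpoint split out according to diabetes type, insulin analogue or use of an insulin pump) will be presented using descriptive statistics".

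The article gives no expected number of pregnancies for any single comparator regimen, and no power for any single component of the composite.

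**The concern.** To call a cohort sufficiently large is to make a statement about sample size. The Discussion attaches it to individual events (malformation, perinatal or neonatal death) and to several regimens. The calculation concerns neither: it uses the union of three outcomes and two groups.

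Two things are at stake.

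- **False reassurance.** This is a post-authorisation safety study requested by a regulator. If the cohort is described as large enough for single rare events, a non-significant difference in one of them may be taken as evidence of safety when a material increase would probably have been missed.
- **Confounding in the regimen split.** Treatment is not assigned, and the plan adjusts the primary contrast because it expects the groups to differ. A descriptive table by analogue or pump has no such protection, yet it is the only planned result in the article that speaks to particular alternatives to detemir.

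**Working it through.** **Inputs.** From Determination of sample size: 1833 evaluable pregnancies, 1:2 split, 80% power, component rates of 4.5% (major malformation), 3% (perinatal death) and 0.9% (neonatal death), and a 3.5-point difference. From Statistical considerations: "tests will be performed as two-sided tests with a significance level of 0.05". The article does not say which group does better.

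**Step 1: the plan's own figures.**

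- Composite event rate under independence: 1 − (1 − 0.045)(1 − 0.03)(1 − 0.009) = 0.0820, so 91.8% are event-free, as stated.
- Group sizes: 1833 / 3 = 611 detemir and 1222 other.
- Required size with 95.3% (detemir) versus 91.8% event-free: n₁ = [1.96·√(p̄(1 − p̄)(1 + 1/2)) + 0.8416·√(p₁(1 − p₁) + p₂(1 − p₂)/2)]² / 0.035², with p₁ = 0.047, p₂ = 0.082 and p̄ = (0.047 + 2 × 0.082)/3 = 0.0703. This gives 598 + 1196 = 1794, within 3% of 1833.
- Exact power of Fisher's test at 611 versus 1222 is 80.3%.

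So 1833 reproduces, for the pooled composite and an improvement with detemir. A 3.5-point worsening would need 2526 (same formula, no continuity correction).

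**Step 2: power formula.** Power = Φ[(|p₁ − p₂| − 1.96·s₀)/s₁], where s₀ = √(p̄(1 − p̄)(1/n₁ + 1/n₂)), p̄ is the size-weighted mean rate, and s₁ = √(p₁(1 − p₁)/n₁ + p₂(1 − p₂)/n₂).

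For the composite at 611 versus 1222: s₀ = 0.01267, s₁ = 0.01162, (0.035 − 1.96 × 0.01267)/0.01162 = 0.875, and Φ(0.875) = 0.81.

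**Step 3: single events, detemir (611) versus the whole pooled group (1222).** The 1.5- and 2-fold multipliers are illustrative and are not in the article.

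| Event | Detemir v other | Power |
|---|---|---|
| Composite, 3.5 points lower | 4.7% v 8.2% | 81% |
| Major malformation, 1.5-fold | 6.75% v 4.5% | 53% |
| Perinatal death, 1.5-fold | 4.5% v 3% | 38% |
| Neonatal death, 2-fold | 1.8% v 0.9% | 40% |

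At the reference rate, expected neonatal deaths are 611 × 0.009 = 5.5 and 1222 × 0.009 = 11.0.

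If each component instead fell in the same ratio as the composite (4.7/8.2 = 0.573), power would be 52%, 36% and 12% for malformation, perinatal death and neonatal death.

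**Step 4: the composite against one comparator regimen.** The regimen size is assumed to be 400 to 611 (about a third to a half of 1222).

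| Direction | Pooled, 1222 | One regimen, 611 | One regimen, 400 |
|---|---|---|---|
| Detemir better (4.7% v 8.2%) | 81% | 70% | 62% |
| Detemir worse (11.7% v 8.2%) | 67% | 53% | 43% |

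Each row has its own pooled starting value. The gap between 81% and 67% comes from the direction of the effect, not from splitting the comparator.

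**The case against.** The strongest defence is that the design and analysis contain no error here. The objective, endpoint, primary test and sample size all name the same contrast, and 1833 reproduces for it. Pooling the alternatives is an openly stated choice in a safety study of one drug, the regimen split is openly labelled descriptive, and the Discussion sentence could be read loosely as detemir against the rest.

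Most of this stands, and it confines the point to the size claim and the regimen split. The loose reading does not rescue the sentence, because it names single events and Step 3 shows these have low power even against the whole pooled group.

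A reader might infer more than the article supports:

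- **That Methods/design makes the same claim.** It says the data collection "will allow comparison and analysis of the occurrence of events between the various insulin treatment regimens". That says nothing of size or power, and a descriptive comparison satisfies it.
- **That the title contradicts the endpoint.** It speaks of detemir "in comparison with other long-acting insulins", but nothing in the article says that this term excludes NPH.
- **That the components will go unreported.** The article lists only key secondary endpoints, and the full protocol or analysis plan, not shown, may cover them.
- **That splitting cuts power from 81% to 43–53% when detemir is worse.** The pooled power in that direction is already about 67%.

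The unseen analysis plan might also add adjusted regimen contrasts. That would not make the published size claim true, and the article itself fixes the split as descriptive.

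**Conclusion.** The point holds as an overstated size claim, together with a regimen split that is weaker than it need be. The article's calculation supports one inference: the composite, detemir against pooled other basal insulins, with about 81% power for a 3.5-point improvement. It does not support the Discussion's statement about single rare events or individual regimens. Power is about 38% to 53% for the illustrated rises in single events, and 43% to 70% for the composite against one regimen, depending on direction and regimen size.

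These figures rest on the article's reference rates, 1833 evaluable pregnancies split exactly 1:2, a two-sided 5% normal approximation without covariate adjustment, the illustrative multipliers and the assumed regimen sizes. A different prescribing mix would move the single-regimen figures.

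A reader might conclude that the primary analysis or the pooling is invalid. The article does not support that: sample size, analysis set and primary test are untouched.

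**What to change.** 1. **Discussion, closing paragraph.** Restrict the size claim to the composite outcome for detemir against pooled other basal insulins, and state that comparisons of individual regimens and individual events are exploratory.
2. **Statistical considerations.** Replace the descriptive-only split by regimen with two pre-specified contrasts, detemir versus NPH and detemir versus other long-acting analogues. Adjust them for the baseline confounders already collected, and report estimates with 95% confidence intervals and no power claim.

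The cost is a few extra model runs on data already being collected, plus rewording. The intervals will be wide, and the statement about what the cohort can show becomes less favourable.
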